#### Economic evaluation

A cost-utility analysis (CUA) and a cost-effectiveness analysis (CEA) will be performed from the societal and the healthcare perspective. From the societal perspective all costs will be taken into account irrespective of who pays or benefits, whereas solely those borne by the healthcare sector will be included when the healthcare perspective is applied [40]. For the CUA and CEA, missing cost and effect data will be imputed using multiple imputation [52]. The results of the imputed datasets will be pooled using Rubin’s rules [52]. In order to account for the highly skewed nature of cost data, bias-corrected and accelerated bootstrapping with 5000 replications will be used to estimate 95% confidence intervals around the mean differences in costs between the study groups. Incremental Cost-Effectiveness Ratios (ICERs) will subsequently be calculated by dividing the differences in costs between study groups by their respective differences in QALYs for the CUA. For the CEA, ICERs will be calculated by dividing the difference in costs by the difference in PA and physical functioning. The uncertainty surrounding the ICERs will be graphically illustrated by plotting bootstrapped incremental cost-effect pairs on cost-effectiveness planes [53]. Moreover, cost-effectiveness acceptability curves (CEACs) will be constructed to provide a summary measure of the joint uncertainty of costs and effects. CEACs indicate the probability of the e-Exercise intervention being cost-effective in comparison to usual care at different willingness-to-pay values [54]. To test the robustness of the study results, several sensitivity analyses will be performed.

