**RCT study procedures.**

### Participants

#### Physical therapists

A stratified random sample of 800 physical therapy practices in three provinces of the Netherlands (e.g. Noord-Holland, Utrecht and Gelderland) will be invited by letter to participate in the study. Contact information of physical therapy practices will be obtained from the national database for physical therapists of the Netherlands Institute for Health Services Research (NIVEL). Additionally, a recruitment advertisement will be placed in the online newsletter of The Royal Dutch Society for Physical Therapy (KNGF). Each participating physical therapy practice will be asked to enroll one or two physical therapists. The researchers will recruit 100 physical therapists. Inclusion criteria for physical therapists will concern: (i) practicing in primary care, (ii) treating at least six patients with OA of the hip and/or knee each year. Physical therapists practicing in another physical therapy practice participating in the study will be excluded.

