#### Patients

In order to include 200 participants, each physical therapist is requested to recruit about two patients. Since the study of Veenhof et al. [27] showed that recruitment of OA patients in the physical therapy practice is difficult and research has shown that different recruitment strategies do not affect treatment outcomes [28], this study uses various recruitment strategies. First, patients with hip and/or knee OA who visit a physical therapy practice will be invited to participate in the study. Second, recruitment advertisements will be placed in local newspapers. Third, information letters and flyers will be sent to general practitioners. Responders to these articles and flyers will be allocated to the nearest participating physical therapist. Eligibility criteria of patients interested in the study concern: (i) age 40–80 years, (ii) OA of the hip and/or knee according to the clinical criteria of the American College of Rheumatology (ACR) [29]. Exclusion criteria will include: (i) being on a waiting list for a hip or knee replacement surgery, (ii) being contra-indicated for PA without supervision, (iii) being sufficiently physically active according to the physical therapist, (iv) participation in a physical therapy and/or PA program in the last six months, (v) no access to internet, (vi) inability to understand the Dutch language. The diagnostic ACR clinical criteria for knee OA are: knee pain and at least three of the following six criteria: age > 50 years, morning stiffness <30 minutes, crepitation, bony tenderness, bony enlargement and no palpable warmth. Diagnostic ACR clinical criteria for hip OA are: hip pain and hip internal rotation < 15 degree and hip flexion ≤ 115 degree; or hip internal rotation ≥ 15 degree and pain on hip internal rotation and morning stiffness of the hip ≤ 60 minutes and age > 50 years [29]. Contra-indications for PA will be determined using the adapted Physical Activity Readiness Questionnaire (PAR-Q) [30]. This questionnaire is used to identify patients for whom PA is inappropriate.

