### Study procedure

Physical therapists willing to participate in the study will be screened on in- and exclusion criteria by a researcher (CK). Cluster randomization will be performed at the level of the participating physical therapy practices that will randomly be assigned to the intervention (e-Exercise) or the control group (usual care) by means of a computer-generated random sequence table. Physical therapists will receive a half day training about e-Exercise and the study procedure (intervention group) or about practicing according to the “KNGF guideline OA hip-knee” [10] and the study procedure (control group). Physical therapists will inform eligible patients about the study and screen them on in- and exclusion criteria. All suitable patients will be stimulated to contact the research team by telephone, e-mail or reply card. After an informative phone call with one of the researchers (CK or DB), interested patients will receive a letter about the trial and a request to complete an informed consent form. Patients recruited by the additional recruitment strategies (i.e. advertisements in newspapers and flyers from the general practitioner) will be informed by the researchers before they visit their physical therapist. Physical therapists in both groups will be asked to record the content of their treatment on a registration form. During the study period, both patient groups will continue their medication and usual care managed by other caregivers.

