#### Usual care

Patients in the control group will receive usual care. For the current study, usual care is defined as any treatment provided by physical therapists. Physical therapists will be encouraged to practice according to the “KNGF guideline OA Hip-Knee” [10]. According to the guideline, the physical therapy treatment comprises the same three elements as e-Exercise: (i) information, (ii) physical exercise and (iii) strength and stability exercises. Practical content considerations can be made by therapists themselves. The number of sessions will differ per patient. From the NIVEL Primary Care Database we know that the average number of physical therapy sessions in patients with OA is 17.1 [33].

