### Sample size

The power calculation is based on a previous multicenter cluster RCT study among patients with hip and/or knee OA [27] and performed for the primary outcome measure physical functioning (power 0.8; alpha 0.05). In this current RCT study, the target sample size will be 200 participants to detect a small to medium effect size (0.2-0.4) in physical functioning at a 2-sided significance level of 0.05 and anticipating on maximum loss to follow up of 20%.

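### The economic evaluation does not carry over the clustering and baseline control of the effectiveness model; it should resample whole practices and adjust QALY differences for baseline utility

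*Protocol article*

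**What the plan says.** Study procedure fixes the unit of allocation: "Cluster randomization will be performed at the level of the participating physical therapy practices".

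Under Statistical analysis, two adjacent sections treat the data differently.

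- **Effectiveness** plans a multilevel repeated-measures model for primary and secondary outcomes. It controls for baseline values and has the therapist as its top level.
- **Economic evaluation** plans multiple imputation of missing costs and effects, pooled by Rubin's rules. For cost differences, "bias-corrected and accelerated bootstrapping with 5000 replications will be used to estimate 95% confidence intervals", and the reason given is that costs are highly skewed. The cost-utility ratio comes from "dividing the differences in costs between study groups by their respective differences in QALYs for the CUA"; the cost-effectiveness ratios use the differences in physical activity and functioning in the same way. Bootstrapped cost-effect pairs then feed the cost-effectiveness planes and acceptability curves.

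The economic section mentions no practice, therapist or cluster and no baseline covariate. Several sensitivity analyses are announced without content. Table 2 lists EQ-5D at 0, 3 and 12 months, so baseline utility will be available.

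**The concern.** The economic section settles the bootstrap type, the number of replications, the pooling rule and the ratio, and skewness is the only feature of the data that it addresses. A bootstrap in its standard form draws patients independently. In a trial that randomises practices, this leaves out the between-practice part of the variance.

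Some clustering of costs is plausible. Under Usual care, "Practical content considerations can be made by therapists themselves", and the number of sessions varies by patient. In the e-Exercise arm therapists may depart from the protocol. Physical therapy sessions are also where the Background expects the saving.

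The QALY is built from utility multiplied by time, so each patient's baseline utility enters it directly and again through its correlation with later utilities. Unless the difference is adjusted, an imbalance at baseline appears as a QALY gain or loss.

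Cost-effectiveness is the second of the trial's two stated hypotheses. An acceptability curve is read as a probability, so overconfidence there goes straight into the conclusion.

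**Working it through.** The economic section gives no precision or power figure, so there is nothing of the plan's own to reproduce on this point. The documents give no ICC, utility SD or correlation either; those below are assumed ranges.

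**1. Patients per practice**

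- Therapists: "The researchers will recruit 100 physical therapists".
- Therapists per practice: "Each participating physical therapy practice will be asked to enroll one or two physical therapists", so 100/2 = 50 to 100/1 = 100 practices.
- Patients: 200 in total, and "each physical therapist is requested to recruit about two patients".
- Patients per practice, m: 200/100 = 2 to 200/50 = 4.

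**2. Effect of ignoring practices**

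Design effect DE = 1 + (m − 1) × ICC. The true SE is √DE times the patient-level SE. Actual coverage of a nominal 95% interval is 2Φ(1.96/√DE) − 1.

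| m | ICC (assumed) | DE | SE factor | Coverage |
|---|---|---|---|---|
| 2 | 0.01 | 1.01 | 1.005 | 94.9% |
| 2 | 0.05 | 1.05 | 1.025 | 94.4% |
| 2 | 0.10 | 1.10 | 1.049 | 93.8% |
| 2 | 0.20 | 1.20 | 1.095 | 92.6% |
| 4 | 0.01 | 1.03 | 1.015 | 94.7% |
| 4 | 0.05 | 1.15 | 1.072 | 93.2% |
| 4 | 0.10 | 1.30 | 1.140 | 91.4% |
| 4 | 0.20 | 1.60 | 1.265 | 87.9% |

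**3. Check by simulation with skewed costs**

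Lognormal costs (log-scale SD 1, ICC on the log scale), 100 patients per arm, 1000 simulated trials, percentile bootstrap (not BCa). Monte Carlo error is about 0.01.

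| m | ICC | Patients resampled | Practices resampled |
|---|---|---|---|
| 2 | 0.05 | 0.926 | 0.934 |
| 4 | 0.05 | 0.910 | 0.921 |
| 4 | 0.10 | 0.888 | 0.908 |
| 4 | 0.20 | 0.879 | 0.922 |

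The direction agrees. Resampling practices recovers part of the loss, but coverage stays below 95%, so clustering is not the only cause of undercoverage in such data.

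**4. Baseline utility in the QALY difference**

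With linear interpolation between 0, 3 and 12 months (assumed), the weights are:

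- month 0: 0.25/2 = 0.125
- month 3: 0.25/2 + 0.75/2 = 0.5
- month 12: 0.75/2 = 0.375

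With equal SDs at each visit and correlation r between baseline and later utility, the share of a baseline difference that passes into the QALY difference is 0.125 + 0.875r:

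- r = 0.4: 0.475
- r = 0.6: 0.650
- r = 0.8: 0.825

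The SE of a chance baseline difference is SD × √(2/n), taken without clustering. The range of n is 100 per arm down to 80 after the protocol's 20% loss. A one-SE imbalance then shifts the QALY difference as follows:

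- smallest case (SD 0.15, n = 100, r = 0.4): 0.15 × √(2/100) = 0.0212; × 0.475 = 0.010 QALY
- largest case (SD 0.25, n = 80, r = 0.8): 0.25 × √(2/80) = 0.0395; × 0.825 = 0.033 QALY

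**5. Whether the Effectiveness section fills the gap**

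Table 2 lists both EQ-5D and OA-related costs as secondary outcomes, so that model nominally reaches them. It is a repeated-measures model of values at each visit. A 12-month QALY is one value per patient and has no baseline counterpart. Costs have their own bootstrapped mean difference in the economic section, and nothing says that the ratios take their inputs from the multilevel model. If they did, its top level is the therapist, whereas the practice is randomised.

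**The case against.** The strongest objection is that the text is silent rather than wrong. It does not say that patients are resampled one by one or that QALY differences are raw, and a reader who infers either as a stated choice goes beyond the document. Resampling unit, covariates and imputation variables are details that an article often leaves to the full plan, and a difference in QALYs may equally be a regression-adjusted one. This stands as a limit on confidence. It does not remove the point: the section is specific about method, gives skewness as the sole reason for it, and follows directly on a section that does handle clustering and baseline values.

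Three further objections hold in part.

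- **Strength of clustering.** It is tempting to say that costs cluster strongly. The documents do not show it. Therapists influence physical therapy sessions, but the cost outcome also covers hospital and specialist care, drugs, informal care, sickness absence and presenteeism. An ICC of 0.30 would be an extreme assumption, and 4 patients per practice requires every practice to supply two therapists. With 2 per practice the loss is small.
- **Chance imbalance is not bias.** Under sound randomisation, an unadjusted difference is unbiased and its interval already contains the variance due to baseline utility. Omitting adjustment then costs precision and does not make the interval too narrow.
- **Imbalance need not be chance.** Therapists are not blinded, and they inform and screen patients once their practice has been allocated. Patients who respond to advertisements or flyers are informed by the researchers first, which narrows this route, but Table 1 still has the therapist assess eligibility. Differential recruitment is a possibility in this design, not something that the documents establish.

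**Conclusion.** The point holds as a weakness in what the economic section provides for, with medium confidence. If the section is carried out with a standard patient-level bootstrap, the cost intervals, planes and acceptability curves will be too confident. Coverage would be about 94.9% to 91.4% for an assumed ICC of 0.01 to 0.10, and about 88% at ICC 0.20 with 4 patients per practice. The clustering effect is therefore small to moderate.

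An unadjusted QALY difference would pass on about 48% to 83% of any baseline utility difference, for an assumed correlation of 0.4 to 0.8. This costs precision where the imbalance is chance and causes bias where it comes from recruitment after allocation. Because the QALY difference is the denominator of the cost-utility ratio, the ratio is sensitive to such shifts when the true difference is small. The documents give no expected QALY difference, so the effect on the ratio itself cannot be sized.

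**What to change.** In the Economic evaluation section, state that:

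- whole practices are resampled within arm in each of the 5000 replications, by a cluster or two-stage bootstrap, for the cost intervals and for the cost-effect pairs behind the planes and acceptability curves;
- the imputation model contains arm and practice (practice as a random effect, since 2 to 4 patients each is too few for separate indicators);
- within each replication, the QALY difference is estimated by regression on baseline EQ-5D utility, and the physical activity and functioning differences by regression on their own baseline values.

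No new data are needed. The cost is a few more lines of plan text and code, and somewhat wider cost intervals. Two limits remain. Adjustment removes only the part of any recruitment imbalance that shows in baseline utility, and with skewed costs and as few as 25 practices per arm some undercoverage may persist.

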### Timeline

Recruitment of physical therapy practices begun in May 2014. The trial will start in September 2014. Until December 2014 patients are able to enrol the program. The follow-up will last until December 2015. Analysis of the data will start in January 2016.

## Discussion

Scarce health resources and a growing number of patients with OA of the hip and/or knee require cost-effective treatment strategies in patients with OA. The presented RCT will study the (cost)-effectiveness of e-Exercise, an intervention in which face-to-face exercise therapy sessions are partly replaced by a web-based PA intervention. This study is, as far as we know, the first RCT that investigates the (cost)-effectiveness of a blended intervention in patients with knee and hip OA. Therefore, this RCT will provide internationally relevant results regarding the short- and long-term (cost)-effectiveness of an exercise therapy intervention that incorporates modern technologies.

The primary goal of e-Exercise is to improve levels of PA and physical functioning in a cost-effective manner. In addition to our outcome measurements, e-Exercise might have several other benefits beyond the primary scope of this study. First, a number of studies showed that exercise therapy may help to postpone joint replacement surgery [55–57]. For example, in the study of Pisters et al. [56], a 60 month follow-up showed that 20% of the patients from the exercise therapy group underwent total hip surgery, compared to 45% of the patients from the usual care group. The exercise therapy consisted of a 12-week Behavioral Graded Activity treatment [27], which is also incorporated in e-Exercise. Second, it is known that most people with OA of the hip and/or knee suffer from at least one comorbidity, such as cardiovascular diseases and diabetes mellitus. It is presumable that improving PA contribute to patients’ general health status, since PA has several health advantages for these comorbidities [58].

Although the study is well-considered, we take into account potential operational issues. First challenge is the recruitment of sufficient numbers of physical therapists. Since e-Exercise is characterized by fewer physical therapy sessions, physical therapists will receive less reimbursement from health insurances compared to usual care. To deal with this challenge, accreditation points for participating physical therapists will be supplied in order to make study participation more attractive. Another incentive is that physical therapists keep their access to the website after the study is finished. The second challenge is the non-usage of the web-based part of e-Exercise. Previous studies have indicated that participants in online interventions are less motivated and feel less pressure to continue compared to traditional face-to-face interventions [59]. However, in order to stimulate website usage, we will incorporate email reminders into the program. But most importantly, since this study concerns a blended intervention, which is a combination of face-to-face contact with e-health, e-Exercise is expected to maximize adherence compared to self-guided internet interventions [17, 23].

There are several strengths in the design of this study. First, we elaborate on the study results of Joint2Move [24]. This intervention showed to be an effective web-based intervention for patients with OA of the hip and/or knee and will be the fundament for e-Exercise. Second, the primary outcome measurements PA and physical functioning will be measured subjectively (questionnaires) and objectively by means of accelerometers and the timed “Up & Go test”. Third, the 12-month follow-up will result in data about long-term effectiveness. The last strength is that e-Exercise will be evaluated in daily physical therapy practice, the setting in which the intervention will be implemented after the presented trial. Therefore, user experiences can be used in order to improve e-Exercise and to facilitate implementation.
